### Sample size calculation

The PASS software (PASS 11, NCSS, LLC, Kaysville, UT, USA) will be used to estimate the sample size utilizing two independent sample means (*α* = 0.05, *β* = 0.10). We will use the mMRC as the primary efficacy outcome. Based on previous clinical studies on the effect of respiratory symptoms after acupressure therapy plus Liu Zi Jue Qigong interventions, the mMRC Scale score in the control group is 0.52 with a standard deviation of 0.11 [27], and the average mMRC Scale score in the treatment group is 0.95 with a standard deviation of 0.92. In this study, the target sample size will be 64 participants in each group, anticipating on maximum loss to follow-up of 20%.

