### Randomization

Randomization will be performed after the eligibility assessment and baseline assessment. The Department of Science and Technology of SUTCM will generate the randomization sequence using a random number generator (IBM, Chicago, IL, USA) and then placed in a sequenced, sealed, opaque envelope. When potential participants meet the inclusion criteria, the envelope can be opened and the subject will accept the corresponding measures. Then, eligible patients will be randomly divided into a guideline therapy group and a guideline therapy plus TCMR group, with an allocation proportion of 1:1.

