### Statistical analysis

#### General analysis principles

Statistical analysis will be performed using IBM SPSS version 25.0 (IBM Corp., Armonk, NY, USA). A Kolmogorov-Smirnov test with Lilliefors correction will be used to analyze all quantitative variables to determine whether they follow a normal distribution. Nonnormally distributed data will be expressed as the median (upper and lower quartiles), and normally distributed data will be expressed as the mean ± the standard deviation (SD). Categorical variables will be presented as frequencies and percentages. The level of significance will be *α* < 0.05 with a two-tailed test, and 95% confidence intervals will be presented where appropriate.

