#### Analysis of primary outcome

The primary outcomes will be evaluated at baseline, 6 days after the intervention, and upon discharge based on the intention-to-treat analysis (ITT). The primary endpoint of the trial is the mean change in mMRC Scales from baseline to the discharge day. Baseline covariates included for adjustment were sex, age category, history of cardiopulmonary disease, and body weight category. The whole outcomes scale was also measured at baseline. When the data have a normal distribution, two-way repeated-measures ANOVA will be used as the main analytic method, and a paired sample *t* test will be used between the two intervention groups; if the normal distribution is not met, the Wilcoxon test will be used as an alternative method. Prior to any analysis, any missing data pattern will be investigated and reasons for missing data obtained and summarized where possible. The percentage of missing data is 20%, and we plan to generate 5 imputed datasets, which is the minimum recommended number [28]. The sensitivity analyses were carried out to assess two assumptions about missing data, and data imputation scenarios can potentially influence the primary result [29]. To account for missing data, our primary analyses were conducted on an imputed data set where missing values were generated using multiple imputation by chained equations (MICE) [30].

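### The primary endpoint is a mean change in mMRC, but the normality gate will almost certainly replace the test of means by a Wilcoxon test, which does not test that endpoint if the arms differ in spread

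*Protocol article*

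**What the plan says.** Under Analysis of primary outcome, the article sets the endpoint as the average change in mMRC between baseline and the day of discharge, analysed by intention to treat with multiple imputation and adjusted for baseline covariates. The choice of test is conditional: "When the data have a normal distribution, two-way repeated-measures ANOVA will be used as the main analytic method". The same sentence adds a paired t test between the two groups, and a Wilcoxon test as the alternative if normality is not met. It does not say whether that is the rank-sum or the signed-rank test.

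The gate is in General analysis principles: a Kolmogorov-Smirnov test with Lilliefors correction is applied to every quantitative variable "to determine whether they follow a normal distribution". No other assumption is checked, and no method that allows unequal variances is named.

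Sample size calculation expects very different spreads. There "the mMRC Scale score in the control group is 0.52 with a standard deviation of 0.11", and "the average mMRC Scale score in the treatment group is 0.95 with a standard deviation of 0.92". The design is randomised "with an allocation proportion of 1:1".

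**The concern.** The endpoint is a difference in means. A rank-sum test asks instead whether a patient in one arm tends to rank above a patient in the other. The two questions coincide when the arms differ only by a shift. They separate when the spreads differ, and then the rank test can be significant although the mean changes are equal.

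Two features of the plan make this more than theoretical. The scale has only grades 0 to 4, so the normality gate is likely to select the Wilcoxon branch. And the planning values say that TCMR changes the spread.

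At stake is the primary p-value: a significant result could not be read as a difference in mean mMRC change. The fallback would also supply no mean difference with a confidence interval, and it has no place for the covariates that the same section says will be adjusted for.

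**Working it through.** **1. The plan's own figure.** Inputs from Sample size calculation: SDs 0.11 and 0.92, means 0.52 and 0.95 (difference 0.43), "utilizing two independent sample means (*α* = 0.05, *β* = 0.10"; two-sided according to General analysis principles; and "the target sample size will be 64 participants in each group, anticipating on maximum loss to follow-up of 20" per cent.

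- Normal approximation: n = (0.11² + 0.92²) × (1.960 + 1.282)² / 0.43² = 48.8, so 49; 49/0.8 = 61.25, so 62.
- Pooled t test: 50; 50/0.8 = 62.5, so 63.
- Welch t test: 51 (power 90.2%); 51/0.8 = 63.75, so **64**.

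The stated 64 is matched exactly by the unequal-variance calculation. The analysis section names no unequal-variance method.

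**2. How far the SDs can be used.** A whole-number variable with mean 0.52 has an SD of at least √(0.52 × 0.48) = 0.50. The 0.11 is therefore doubtful. The checks in step 4 replace it by 0.51 or 0.52 (close to the floor) and by 0.70 (a milder contrast), against 0.92.

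**3. Will the gate select the Wilcoxon test?** Lilliefors test, n = 64, assumed whole-grade data:

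- scores with mean 0.95 and SD 0.92: normality rejected in 300 of 300 samples;
- changes from an assumed baseline (mean 2.0, SD 0.9) to such scores: rejected in 300 of 300;
- rounded whole-grade changes with SD 0.6, 0.92 or 1.2: rejected in 100%.

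**4. The rank-sum test at equal means.** One example shows the mechanism. Two 0-4 distributions, both with mean 0.52:

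| Grade | 0 | 1 | 2 | 3 | 4 |
|---|---|---|---|---|---|
| A, SD 0.52 | 0.490 | 0.499 | 0.010 | 0.000 | 0.000 |
| B, SD 0.92 | 0.682 | 0.193 | 0.071 | 0.034 | 0.021 |

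P(A > B) = 0.499 × 0.682 + 0.010 × (0.682 + 0.193) = 0.349. P(A = B) = 0.490 × 0.682 + 0.499 × 0.193 + 0.010 × 0.071 = 0.431. The rank-sum target is 0.349 + 0.431/2 = 0.565, not 0.5, although the means are equal. With these two distributions the rank-sum test was significant in 31.6% of trials at 64 per arm and 25.8% at 51 per arm; Welch gave 5.7% at both sizes.

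Rejection at a nominal 5%, 64 per arm, discrete distributions fitted to the mean and SD, 8,000 trials per setting (a 3,000-trial repeat in brackets):

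| Common mean | Rank-sum, SD 0.51 v 0.92 | Rank-sum, SD 0.70 v 0.92 |
|---|---|---|
| 0.52 | 32.0% (32%) | 12.4% (13%) |
| 0.75 | 19.7% (21%) | 9.6% (10%) |
| 0.95 | 11.8% (12%) | 7.8% (8%) |

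Welch in the same six settings: 4.8% to 5.5% (repeat 5.1% to 6.0%). With normal data at the plan's literal SDs of 0.11 and 0.92, rank-sum gave 9.1% and Welch 4.9%.

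**5. The ANOVA branch.** Normal data, SD 0.11 v 0.92, equal means:

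- pooled test: 5.1% at 64 per arm and at 51 per arm;
- repeated-measures group-by-time test (three visits, compound symmetry, assumed correlation 0.5): 5.2% and 5.3%.

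It moves only when the analysed arms differ in size: 8.3% with 64 control v 51 TCMR, and 3.0% the other way round. With SD 0.51 v 0.92 the same splits give about 6.2% and 3.5%; with 0.70 v 0.92, about 5.5% and 4.1%.

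**The case against.** A reader might infer that the 5% error rate of the whole primary analysis fails because the named tests assume equal spread. The documents do not support that. Three tests are named, and the paired t test makes no equal-spread assumption (its use between independent arms is a separate matter). The ANOVA keeps about 5% at 1:1 allocation, and intention to treat with multiple imputation keeps the analysed arms near that ratio. The 8.3% and 3.0% figures need the full 20% loss in one arm, no imputation, and an SD that whole grades cannot produce.

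Three further points stand.

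- If TCMR affects nobody, randomisation gives both arms the same distribution and the rank-sum test keeps 5%. The inflation needs an effect on spread that leaves the mean unchanged.
- The planning SDs are described as scores, not changes, and come from a source not shown. The spread of change by arm is never stated. The 0.51 lies almost on the floor: at mean 0.95 it puts about 87% of controls in grade 1. The eight-fold ratio should not be taken at face value.
- Everything in step 4 rests on reading Wilcoxon as rank-sum.

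It can also be said that handling of variances belongs in an analysis plan that is not shown. That does not dispose of the point. The article itself fixes both the endpoint and the rule that switches the test, and the two do not match.

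**Conclusion.** The point holds for the Wilcoxon fallback. The article promises inference on a mean change, and its gate leads almost surely to a test that does not address a mean when spreads differ, gives no mean difference, and cannot hold the stated adjustment.

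Size: at equal means with unequal spread, about 12% to 32% of trials significant at SD 0.51 v 0.92 and about 8% to 13% at 0.70 v 0.92, against about 5% for Welch. This rests on the rank-sum reading, assumed 0-4 whole-grade distributions, 64 per arm, and score SDs standing in for change SDs. The exact size is therefore uncertain; the mismatch between endpoint and test is not. It is not a finding against the ANOVA at equal arm sizes, nor a claim of excess false positives when treatment does nothing. It should be corrected before the analysis.

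**What to change.** Replace the normality-dependent switch by one primary method, used whatever the normality test says. Within each multiply imputed data set, regress mMRC change to discharge on arm, baseline mMRC and the covariates the article names (sex, grouped age, grouped body weight, cardiopulmonary history), with heteroscedasticity-robust (HC3) standard errors. Combine across imputations and report the adjusted difference in mean change with its 95% confidence interval. A bare Welch test would also allow unequal spread but would drop the adjustment.

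Keep the rank test as a sensitivity analysis only, and say that it is the rank-sum test. The repeated-measures analysis over the three visits can stay as supporting evidence.

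The cost is a short rewrite of the primary-analysis paragraph and a slight loss of power if the spreads prove equal. No extra patients or data are needed.

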### Primary outcome measurements

#### Modified Medical Research Council (mMRC) Dyspnea Scale

We will use the mMRC as the primary outcome indicator to evaluate the dyspnea symptoms and physical health; this scale is a good indicator of the functional capacity of patients’ lungs [22]. Evaluation of the outcomes will occur at three points (before treatment, the 7th day during hospitalization, and the discharge day). The mMRC [22, 23] grades are as follows: mMRC grade 0, dyspnea occurs only during strenuous exercise; mMRC grade 1—the patient has shortness of breath when walking on flat ground or walking on a small slope; mMRC grade 2—due to shortness of breath, when walking on flat ground, the patient is slower than another person of the same age or needs to stop to rest; mMRC grade 3—when walking on flat ground for approximately 100 m or after a few minutes, the patient needs to stop to pant; and mMRC grade 4—due to severe breathing difficulties, the patient cannot leave the house or has breathing difficulties when dressing or undressing. We will assess the mMRC with a repeated longitudinal analysis.

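### The declared main method, a repeated-measures ANOVA, does not test the stated primary endpoint (mMRC change from baseline to discharge), and the plan does not say which result decides

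*Protocol article*

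**What the plan says.** All references are to the protocol article.

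- Analysis of primary outcome, endpoint: "The primary endpoint of the trial is the mean change in mMRC Scales from baseline to the discharge day".
- Same section, assessments: "The primary outcomes will be evaluated at baseline, 6 days after the intervention, and upon discharge".
- Same section, method under normality: "two-way repeated-measures ANOVA will be used as the main analytic method", with the addition that "a paired sample *t* test will be used between the two intervention groups".
- Same section, otherwise: "if the normal distribution is not met, the Wilcoxon test will be used as an alternative method".
- Under the mMRC outcome: "We will assess the mMRC with a repeated longitudinal analysis".
- General analysis principles: "The level of significance will be *α* < 0.05 with a two-tailed test". The same section has a Kolmogorov-Smirnov test with Lilliefors correction judge the normality of every quantitative variable.
- Sample size calculation: PASS is used to "estimate the sample size utilizing two independent sample means", that is, for a single between-arm comparison.

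No section says which ANOVA effect is decisive, or at which time point or on which contrast the t or Wilcoxon test is made.

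**The concern.** The endpoint is one number per patient: discharge grade minus baseline grade. A two-way (group by time) ANOVA over three assessments gives two between-arm results, and neither is the between-arm difference in that number.

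- **Group main effect.** It compares the arms on the mean of all three assessments. Randomisation follows the baseline assessment (Randomization section), so no treatment effect can exist at baseline. Including baseline dilutes any effect at discharge.
- **Group-by-time interaction.** With three time points it has 2 degrees of freedom and asks whether the arms' profiles differ anywhere. A difference confined to mid-stay is enough.

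The trial could therefore be reported as positive on its primary outcome with no difference in change to discharge. With no deciding effect named, the choice among p-values could also be made after they are seen. The t test does not settle this: it is called paired although the arms are independent, and it has no stated contrast. The Wilcoxon alternative has the same gap.

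**Working it through.** **Inputs from the article:** 64 per arm; expected loss 20%; means 0.52 and 0.95, so a difference of 0.43 (only its size is used here); SDs 0.11 and 0.92; two-sided 0.05; power 90%.

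**Assumptions, not in the article:** normal data, equal correlation r between visits of 0.3, 0.5 or 0.7, and the two effect patterns below.

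**1. The plan's own figure.** Root-mean-square SD = √((0.11² + 0.92²)/2) = √0.42925 = 0.655. For a difference of 0.43, the unequal-variance t test needs 51 per arm (power 90.2%), and 51/0.8 = 63.75, rounded up to 64. The stated 64 is reproduced, but for one two-sample comparison and not for the ANOVA.

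**2. Difference at mid-stay only.** True between-arm differences are 0, 0.43, 0 at baseline, mid-stay and discharge. Their mean is 0.1433, so the deviations are −0.1433, 0.2867, −0.1433, with sum of squares 0.1233. The interaction's noncentrality is

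λ = (n/2) × (sum of squared deviations) / (SD² × (1 − r)), with 2 and 2(2n − 2) df.

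For n = 64, SD 0.92 and r = 0.5: λ = 32 × 0.1233 / (0.8464 × 0.5) = 9.32 on 2 and 252 df, which gives 78%.

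| r | λ | Interaction p < 0.05 | Test of change to discharge p < 0.05 |
|---|---|---|---|
| 0.3 | 6.66 | 63% | 5% |
| 0.5 | 9.32 | 78% | 5% |
| 0.7 | 15.53 | 95% | 5% |

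Simulation agrees (62–95%). At 51 per arm the interaction figures are about 52%, 68% and 89%. With SD 0.655 and 64 per arm they are 91%, 98% and 99.9%. The direction does not depend on the choice of SD.

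**3. No effect anywhere.** Under these assumptions the group and interaction tests are independent, so the chance that at least one is significant is 1 − 0.95² = 9.75%. Simulation gives about 10% at each r. Adding a t test on change to discharge raises it to about 12%. One pre-specified contrast stays at 5%.

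**4. A real effect growing to discharge** (differences 0, 0.215, 0.43; 64 per arm, r = 0.5).

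| SD | Group effect | Interaction | Stated contrast |
|---|---|---|---|
| 0.92 | 36% | 65% | 75% |
| 0.655 | 62% | 92% | 96% |

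**5. Which branch will run.** mMRC takes five values, 0 to 4. In simulated rounded grades (assumed means 0.52 to 2.5, SD 0.92) and change scores, with 51, 64 or 128 values, the Lilliefors test rejected normality in 500 of 500 samples in every setting. On the plan's own rule the Wilcoxon test would then very probably replace the ANOVA.

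**The case against.** The strongest reply is that the criticised model will probably never run. The ANOVA and t test apply only if normality holds, and a five-grade scale will almost surely fail the check. The Wilcoxon branch has no group main effect and no omnibus interaction. This stands, and it limits the ANOVA figures to the ANOVA branch. It does not rescue the plan: the article declares the ANOVA its main method, and the Wilcoxon test has no stated contrast, time point or version. The deciding comparison is unfixed in both branches, and which branch applies depends on the data.

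A second reply is that the article ranks the ANOVA first and names one endpoint, so reading out the right contrast can be left to the SAP. A reader might infer that the plan lets any p-value carry the claim; it does not say so, and the 10% and 12% are conditional on that use. But this is more than an omitted detail. The endpoint and the main method are both stated, and they do not correspond.

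Third, the article does not say that all three assessments enter the ANOVA. With baseline and discharge only, the interaction is identical to the t test on change. Three levels is the natural reading of the listed assessments and of the longitudinal analysis under the mMRC outcome, but it remains a reading.

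Two stronger inferences are not supported. An error rate of about 16%, three times nominal, needs separate t tests at mid-stay and at discharge, which no section plans. A large power loss as a general result needs SD 0.92 in both arms, whereas the article gives 0.11 and 0.92. At the root-mean-square SD the interaction loses only about 4 points against the stated contrast (92% against 96%).

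**Conclusion.** The point holds as a mismatch between two stated rules: the primary endpoint is a single contrast to discharge, and the declared main method, on its natural three-assessment reading, does not test it. No section says which ANOVA effect decides, and the t test and Wilcoxon alternative are equally unfixed.

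In the ANOVA branch, a mid-stay-only difference of 0.43 makes the interaction positive in 62–95% of trials (64 per arm, SD 0.92, correlation 0.3–0.7), against 5% for the stated contrast. If either ANOVA between-arm effect may carry the claim, the false-positive rate is about 10%, or about 12% with a t test on change, against 5%.

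The percentages rest on normal data and assumed correlations. The mid-stay-only pattern is hypothetical, since the intervention continues until discharge. The direction holds over the whole range tried. The conclusion that the deciding comparison is not fixed needs none of these assumptions.

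**What to change.** State under Analysis of primary outcome that the trial is decided by one two-sided 5% test of the between-arm difference in mMRC change from baseline to the discharge day, reported with its 95% confidence interval. Choose the test in advance and do not let a normality test switch it. Either of these would serve:

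- ANCOVA of discharge mMRC on arm, baseline mMRC and the covariates already listed; or
- if a repeated-measures model is kept, the single group-by-discharge contrast from that model.

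Label the group main effect, the omnibus interaction, any mid-stay comparison and any rank-based test (in its independent-samples form) as supportive or sensitivity analyses. Drop the word paired from the between-arm test.

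This is a change of wording, with no added patients or data. The downside is that a mid-stay or omnibus result can no longer be claimed as the primary finding.

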
## Methods/design

### Study design

This will be a single-center, parallel-arms, superiority randomized controlled trial (RCT). The protocol was registered with the China Clinical Trial Registry (item number: ChiCTR2000029994), and the trial protocol was approved by the Ethics Committee of Huangshi Hospital of Traditional Chinese Medicine (item number: HSZYYJ-2020-003-01). A total of 128 patients will be recruited from the Huangshi Hospital of Traditional Chinese Medicine in Hubei province. Written informed consent will be provided by all patients at the time of recruitment. Patients with severe pneumonia symptoms will be recruited and will have equal chances of being allocated randomly to guideline therapy or guideline therapy plus TCMR. Due to the limitations of the intervention methods, only the outcome assessors and statisticians will be blinded. The assessor will perform evaluations and analysis of the outcomes at three points (before treatment, the 7th day during hospitalization, and the discharge day). Data management and statistics will be conducted at the Rehabilitation Medical College of Shanghai University of Traditional Chinese Medicine (SUTCM). The flow chart in Fig. 1 illustrates the study design, and Fig. 2 shows the study schedule. Additional file 1 shows the Standard Protocol Items: Recommendations for Interventional Trials (SPIRIT) checklist.

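### A paired t test is specified between two independent arms, and the normality gate will very likely send mMRC to an unspecified Wilcoxon test that cannot deliver the stated adjusted mean change

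*Protocol article*

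**What the plan says.** The Study design section describes a single-center superiority trial with parallel arms. The Randomization section assigns individual patients "with an allocation proportion of 1:1" and mentions no matching. The Sample size calculation section sizes the trial "utilizing two independent sample means (*α* = 0.05, *β* = 0.10".

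The Analysis of primary outcome section defines the endpoint as the mean change in mMRC from baseline to discharge. It lists four adjustment covariates (sex, age category, history of cardiopulmonary disease, body weight category) and bases the primary analysis on multiply imputed data under intention to treat. If the data are normal, two-way repeated-measures ANOVA is the main method and "a paired sample *t* test will be used between the two intervention groups". Otherwise, "if the normal distribution is not met, the Wilcoxon test will be used as an alternative method".

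Normality is judged under General analysis principles: "A Kolmogorov-Smirnov test with Lilliefors correction will be used to analyze all quantitative variables". The mMRC section defines five whole-number grades, 0 to 4. The secondary outcomes are to follow a similar approach.

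**The concern.** A paired test needs a link between each treated patient and one control patient, and this design has none. The analysis therefore contradicts both the design and the basis of the sample size.

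The gate adds a second problem. A five-grade score is far from normal in the sense that a Lilliefors test detects, so the data are likely to be diverted from the named main method to a test whose form is not given. That test has no place for the covariates and does not estimate a mean change. The analyst would then have to choose the actual primary test after the data are in, which a pre-specified plan is meant to prevent.

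**Working it through.** **1. The plan's own sample size treats the arms as independent.** Inputs from the Sample size calculation section: means 0.52 and 0.95 (difference 0.43), SDs 0.11 and 0.92, α = 0.05, power 90%, loss 20%. The two-sided test comes from General analysis principles.

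- Average variance = (0.11² + 0.92²)/2 = (0.0121 + 0.8464)/2 = 0.42925, so SD = 0.655.
- Normal approximation: n = 2 × (1.960 + 1.282)² × 0.42925 / 0.43² = 48.8, so 49 per arm; 49/0.8 = 61.25, so 62.
- Noncentral t with pooled df: 50 per arm; 50/0.8 = 62.5, so 63.
- Noncentral t with unequal variances (Welch): 51 per arm; 51/0.8 = 63.75, so **64**, the stated figure.

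The independent-samples Welch test has 90.2% power at 51 per arm and 95.5% at 64.

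**2. What a paired t test does on independent arms** (simulated normal data):

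- Unequal arm sizes: it cannot be computed without discarding patients, against the intention-to-treat commitment.
- Equal sizes, random pairing: type I error about 5%; power at 51 per arm 90.4%, against 90.8% for the independent-samples test.
- One data set with 51 per arm: independent-samples p = 0.105. Over 5,000 re-pairings of the same data, the paired p ran from 0.022 to 0.189 (central 95%: 0.063 to 0.150).
- Both arms sorted by value before pairing: type I error about 73%.

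**3. The normality gate, raw grades.** With five grades, at least one holds 20% or more of the patients. The empirical distribution function then jumps by at least 0.20 and lies at least 0.10 from any normal curve. The 5% Lilliefors critical value is about 0.886/√n: 0.124 at n = 51, 0.111 at n = 64, 0.078 at n = 128. At n = 128, five-grade data must therefore fail. Per arm, simulated whole-number 0–4 scores failed in every run at n = 51 and n = 64.

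**4. The normality gate, change scores.** The article gives no SD for the change. I took 0.92 (the treatment-arm score SD) as one value and 0.7 to 2.0 as an assumed range, with an assumed mean change of −1. For a rounded normal change with SD 0.92 the distance from normality is 0.207, above all three critical values. Simulated rejection (1,000 runs per cell), with the second figure treating 20% of values as continuous imputations:

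| SD of change | n = 51 | n = 64 | n = 128 |
|---|---|---|---|
| 0.7 | 100% / 100% | 100% / 100% | 100% / 100% |
| 0.92 | 100% / 99.9% | 100% / 100% | 100% / 100% |
| 1.2 | 100% / 97% | 100% / 99.5% | 100% / 100% |
| 1.5 | 99% / 86% | 100% / 92% | 100% / 100% |
| 2.0 | 88% / 62% | 93% / 70% | 100% / 99.8% |

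**5. What the fallback can deliver.** A plain Wilcoxon test, rank-sum or signed-rank, has no covariate terms, and its result is not a difference in mean change. The same section promises both an adjusted analysis and a mean-change endpoint.

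**The case against.** The paired wording may be a slip, and the two faults partly offset each other: if the gate fails, the paired t test is never run. If the Wilcoxon test is then the rank-sum form, the between-arm test is valid. This stands. A reader might infer that the Wilcoxon test must be paired because it replaces a paired test, and so that the primary result is bound to be invalid. The text does not support that: the Wilcoxon test replaces the whole normal-data plan, ANOVA included, and the secondary-outcome section speaks of differences between arms. The form is unspecified, not wrong.

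A reader might also infer that the gate always fails and the ANOVA is never used. For change scores the table shows otherwise at larger assumed SDs, most clearly with continuous imputed values.

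Nor does the ANOVA miss the endpoint by nature. Its baseline-to-discharge group-by-time contrast is the difference in mean change, with an estimate and standard error that can be pooled. How pooling is done is commonly left to an analysis plan, so silence on it is no fault here.

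Finally, the average cost of random pairing is small: 50 instead of 100 df moves the critical t only from about 1.98 to 2.01. The harm is an arbitrary p-value and possible loss of patients, not a general loss of power.

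**Conclusion.** The point holds in this form. The paired t test between arms is wrong as written, and this rests on the text alone. The Wilcoxon alternative is ambiguous. The gate will very likely divert mMRC from the named main method: in 99.9% or more of samples at SD 0.92, and in 97% or more up to SD 1.2. With 20% continuous imputed values at 51 to 64 patients, the rate falls to 86–92% at SD 1.5 and 62–70% at SD 2.0. These rates rest on assumed change SDs, an assumed mean change and a rounded-normal model. The secondary scales were not simulated, so no rate is claimed for them; the paired-test wording reaches them through the similar approach. The documents do not show that the final primary test will be invalid. They show that no single usable primary analysis is fixed, and this should be corrected before the data are locked.

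**What to change.** In the Analysis of primary outcome section, delete the paired t test and stop using a normality test to choose the primary analysis. Name one between-arm analysis: ANCOVA of discharge mMRC on arm, baseline mMRC and the four covariates already listed, with robust standard errors. Using change to discharge as the response gives the same arm coefficient, because baseline is in the model. Combine the arm difference and its 95% CI over the imputed datasets by Rubin's rules. Name the independent-samples Wilcoxon rank-sum (Mann-Whitney) test as a sensitivity analysis. Replace the paired test in the same way for the secondary outcomes.

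The cost is wording only. The data are already being collected, and the target stays at 64 per arm because it was derived for an independent-samples comparison. The Quality control section provides an amendment route, and the Blinding section keeps the statisticians masked until data lock, so the change can be made without knowledge of results.

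### The primary MICE analysis is fixed at 5 imputed datasets; the test stays valid, but avoidable imputation noise can change the verdict when p is near 0.05

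*Protocol article*

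**What the plan says.** The Analysis of primary outcome section defines the endpoint: "The primary endpoint of the trial is the mean change in mMRC Scales from baseline to the discharge day". On missing data it says "The percentage of missing data is 20" per cent and continues "we plan to generate 5 imputed datasets, which is the minimum recommended number". It makes imputation part of the main result: "our primary analyses were conducted on an imputed data set where missing values were generated using multiple imputation by chained equations". The Sample size calculation section uses the same 20% but as an upper limit: "anticipating on maximum loss to follow-up of 20" per cent. Testing is two-sided at 0.05 (General analysis principles). Secondary outcomes are to be handled in a similar way, so the choice carries over to them. The sensitivity analyses that are mentioned concern missing-data assumptions and imputation scenarios, not the number of imputations.

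**The concern.** The number of imputations is stated in the text, for the primary analysis, at a value that the protocol itself calls a minimum. It is therefore a choice that can be reviewed, not a detail left to an analysis plan that is not shown.

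Multiple imputation draws random values. With few draws, imputing the same data again gives a visibly different estimate, standard error and p value. Relative efficiency, the usual argument for a small number, measures average loss of precision. It does not say how far one reported result can move between runs. At stake is whether a primary result near the 0.05 threshold could be reproduced from the same locked data by someone following the same plan.

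**Working it through.** **Inputs from the protocol.** m = 5 imputations; 20% missing; 64 per arm; 1:1 allocation; two-sided alpha 0.05; power 90%; means 0.52 (SD 0.11) and 0.95 (SD 0.92).

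**Assumed, not in the protocol.** Fraction of missing information (FMI) 0.2, range 0.1 to 0.3; correlation between visits 0.3 to 0.7; discharge scores missing completely at random; mMRC treated as normal.

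**The plan's own figure.** The protocol gives no figure for imputation error. The sample size that frames the simulation does reproduce. The difference is 0.95 − 0.52 = 0.43, and the root-mean-square SD is sqrt((0.11² + 0.92²)/2) = 0.655. An unequal-variance t test at 90% power needs 51 per arm, and 51/0.8 = 63.75, so 64. The standardised design effect is 0.43/0.655 = 0.66.

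**Formulas.** Under Rubin's rules the total variance is T = W + (1 + 1/m)B, with W the within-imputation and B the between-imputation variance. Relative efficiency is 1/(1 + FMI/m). The Monte Carlo SD of the pooled estimate, as a share of its standard error, is about sqrt(FMI/m).

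| FMI | Relative efficiency, m = 5 | Noise, m = 5 | Noise, m = 20 | Noise, m = 50 |
|---|---|---|---|---|
| 0.1 | 0.98 | 0.14 SE | 0.07 SE | 0.045 SE |
| 0.2 | 0.96 | 0.20 SE | 0.10 SE | 0.063 SE |
| 0.3 | 0.94 | 0.24 SE | 0.12 SE | 0.077 SE |

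**What 0.20 SE means near the threshold.** A two-sided p of 0.03 is z = 2.17, which is 2.17 − 1.96 = 0.21 above the cut-off, about one Monte Carlo SD at m = 5. That alone gives about a 15% chance of crossing. The simulated chance is higher because B is estimated on only 4 degrees of freedom (coefficient of variation sqrt(2/4) = 0.71), so the standard error moves too, and the reference t distribution has fewer degrees of freedom.

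**Simulation for a given dataset.** 64 per arm, 20% of discharge scores missing, imputation from arm, baseline and day-7 score, baseline-adjusted comparison, Rubin's rules with small-sample degrees of freedom, visit correlation 0.5. Chance that one run gives p of 0.05 or more, by the p value reached with very many imputations:

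| Converged p | m = 5 | m = 20 | m = 50 |
|---|---|---|---|
| 0.05 | 56% | 53% | 50% |
| 0.03 | 28% | 5% | 0.5% |
| 0.02 | 14% | 0.4% | 0% |
| 0.01 | 4% | 0% | 0% |
| 0.005 | 0.9% | 0% | 0% |
| 0.001 | 0.1% | 0% | 0% |

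At a converged p of 0.03 the 5th to 95th percentile of p is 0.012 to 0.091 with m = 5. Separate simulations with SD 0.92 and visit correlations of 0.5 to 0.6 gave 24 to 26% with m = 5 and about 1% or less with m = 50.

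**Simulation over all trials.** Share in which two independent runs on the same data disagree on significance, for visit correlations 0.3, 0.5 and 0.7 (1,500 trials per cell at m = 5, 600 at m = 50):

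| True effect | m = 5 | m = 50 |
|---|---|---|
| Design (0.66 SD) | 6.0%, 3.1%, 0.3% | 2.3%, 0.5%, 0.0% |
| About half (0.33 SD) | 11.6%, 11.6%, 10.3% | 5.2%, 4.2%, 2.2% |
| None | 3.2%, 3.3%, 3.3% | 1.0%, 1.2%, 1.7% |

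A separate simulation put the lower end at m = 5 at about 2%. The rejection rate under no effect with m = 5 was 4.9% to 5.6%, and the mean estimated FMI was 0.19 to 0.21.

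**The case against.** The strongest reply is that nothing is invalid. Rubin's rules already include the B/m term and adjust the degrees of freedom, so the p value from five imputations is honest, there is no bias, and little power is lost. The protocol also discloses that 5 is a minimum and cites a source for it. All of this stands. A reader might infer that five imputations inflate type I error or distort the treatment effect; the calculations show neither.

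A second reply is that the striking percentages are conditional on a borderline result. That also stands. A reader might infer that the primary p value is not reproducible in general. It is not so: at a converged p of 0.005 or below the verdict flips in 1% of runs or fewer, and at the design effect two runs disagree in 0.3 to 6% of trials. At a converged p of exactly 0.05 no number of imputations settles the verdict; that part comes from the threshold itself.

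A third tempting inference is that, because participants and therapists are unblinded, the seed could be picked to favour an arm. The protocol does not support this. Its Blinding section keeps statisticians unaware of assignment during analysis, and its Data collecting and monitoring section has an independent, supervised statistician analyse locked data. Nor is the lack of a stated seed a fault in itself, since that is commonly left to the analysis plan.

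Finally, FMI, visit correlations, missingness mechanism and normality are assumptions. The simulated baseline-adjusted comparison is not the repeated-measures ANOVA or Wilcoxon test that the protocol names, and with less than the maximum 20% missing the noise shrinks. This limits the precision of the figures. It does not alter the direction: five imputations give more run-to-run noise than fifty, and nothing is gained in return.

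**Conclusion.** The point holds as a moderate, inexpensively removed reproducibility weakness in a choice that the protocol states. It is not an error of validity. With FMI at 0.2, Monte Carlo noise in the primary estimate is about 0.20 SE (0.14 to 0.24 for FMI 0.1 to 0.3) at m = 5, against about 0.06 SE at m = 50. It matters mainly for a converged p of roughly 0.01 to 0.10; at about 0.03 around a quarter of single runs would lose significance, against about 1% with 50. Averaged over trials, disagreement between two runs is about 2 to 3% under no effect and at most about 12% at intermediate effects, falling to about 1 to 5% with 50. The exact percentages depend on the assumptions listed in the working.

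**What to change.** In the Analysis of primary outcome section, change the number of imputed datasets from 5 to 50, and state that the random seed is set before the analysis is run. Secondary outcomes follow, since they use a similar approach. Conduct, sample size and data collection are untouched; the cost is one line of text and slightly more computing time.
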